#### Primary and secondary analysis populations

In this study, all CP patients who meet the inclusion criteria, regardless of their time since diagnosis, are eligible for participation. However, the primary analysis study population consists of patients with a time since diagnosis ≤ 3 years at the start of the intervention. This population is chosen since in these patients the intervention is intended to start early after diagnosis and the investigators postulate that the impact of the intervention may depend on the time since diagnosis. Secondary analysis populations include patients with a time since diagnosis between 4 and 10 years and > 10 years and the total population.

#### Baseline values

Baseline criteria (i.e., at time of inclusion) are age, sex, center, nicotine and alcohol use, co-morbidity, etiology of CP, disease duration, prior endoscopic- and surgical interventions, pancreatic function, and medication use. Baseline values will be analyzed and reported using standard descriptive statistics.

Categorical data will be presented in numbers and percentages. Continuous variables will be summarized as mean with standard deviation (SD) or median with interquartile range (IQR) depending on normality of distribution. Missing baseline data will be handled by using multiple imputation techniques using the fully conditional specification method (aka “chained equations”) assuming data are Missing At Random (MAR). The number of required imputations will be based on the two-stage calculation using a quadratic rule [25]. Missing outcome data will not be imputed; the mixed-effects linear regression analysis is valid despite missing values when assuming MAR.

#### Primary outcomes

The two co-primary outcomes of this study are mean difference in QoL (PANQOLI) and level of pain (Izbicki Pain Score) at 12 months after the end of the transition period for each cluster (intention-to-treat analysis) and at 12 months after start intervention for the individual patient defined as the first outpatient clinic visit after the kick-off meeting has been performed (per-protocol analysis).

For the primary outcomes, analyses will be performed using a mixed-effects linear regression analysis, whereby the intervention is compared to current practice (control). The model includes time since diagnosis in years, intervention (yes/no), and time since intervention in years (which will be zero for observations in the control group). Thus, the intervention effect will be modelled as an interrupted time series analysis with a step-change and a slope-change. When appropriate, patient factors collected at enrolment known to predict QoL and pain, respectively, will be included as co-variates. The estimated effect of the intervention at 12 months after the start of the intervention will be expressed as the sum of the step-change and the slope-change. The confidence interval will be derived using the delta method, i.e., adding up the variances and 2 times the co-variance of the estimated step- and slope-change to derive the variance of the total intervention effect. The step-change and slope-change will be separately reported. The Bonferroni correction method will be used to adjust for multiple testing. For the co-primary endpoint, a two-sided alpha < 0.025 will be considered statistically significant. Effect estimates for the primary endpoints will be presented with 97.5% confidence intervals.

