### Study design and setting

The COMBO trial is a nationwide stepped-wedge cluster-randomized controlled superiority trial enrolling CP patients who are receiving active treatment in one of the participating hospitals at time of inclusion. In total, 26 centers of the Dutch Pancreatitis Study Group (DPSG) are participating in this trail. In a stepwise manner, an evidence-based algorithm for the treatment of CP is implemented in all participating centers. Participating centers are divided into 6 clusters, based on location and referral pattern for patients with CP according to the current situation in the Netherlands. Each cluster contains 4 or 5 DPSG centers, among which at least one academic or non-academic teaching hospital and its regional affiliated (non-)teaching hospitals. At the start of the trial, all clusters continue current practice (i.e., control) for at least 6 months, which is considered as the baseline period. Thereafter, clusters are randomly assigned to unidirectional cross-over to the intervention period (i.e., care according to the evidence-based algorithm) at 2-month intervals. Following this fashion, the trial proceeds until all clusters have crossed over to the intervention phase and delivered the intervention for at least 18 months. Total duration of this trial is 35 months (see Fig. 2).

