**Fig. 2 Fig2:**
[figure not shown]
Stepped-wedge design with 6 cluster groups. No cluster groups receive the intervention at baseline (6 months); all cluster groups start with continuing current practice. Cluster groups are randomly assigned to unidirectional cross-over to receive the intervention at 2-month intervals. Total trial duration will be a maximum of 35 months; a baseline period of 6 months, a current practice period of varying in length, a transition period of 1 month, an intervention period of 12 months, and a follow-up period with a minimum duration of 6 months for those patients participating in the per-protocol analysis

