### Statistical analysis

To evaluate the effect of this algorithm in terms of improving QoL and reducing pain severity, the scores of patients before implementation of our algorithm (i.e., current practice) will be compared to those of patients obtained after implementation of the integrated management algorithm. The effect of the intervention will be measured in all participants according to the intention-to-treat principle, meaning that patients will be analyzed as exposed to the intervention according to the order and dates of the randomization schedule. Secondary analyses include a per-protocol analysis in which the outcomes of patients actually receiving the intervention (defined as an outpatient clinic visit within ≤ 6 months after the cluster has switched over to the intervention) will be evaluated. The effect of the intervention will be expressed as a step-change (i.e., immediate effect of the intervention) and slope-change (i.e., effect of the intervention on the secular trend). Time is a potential confounder and changes external to the trial may create underlying secular trends. Therefore, analyses will be adjusted for time effects irrespective of their statistical significance.

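### The primary model lists no calendar-time term although the plan promises time adjustment; fitted as listed, it would count most of a calendar jump after month 16 as treatment effect at 12 months

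*Protocol article*

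**What the plan says.** Study design and setting and the Fig. 2 legend fix the timetable. "Participating centers are divided into 6 clusters", all start with 6 months of current practice, and then "Cluster groups are randomly assigned to unidirectional cross-over to receive the intervention at 2-month intervals". The legend adds "a transition period of 1 month, an intervention period of 12 months" and at least 6 months of further follow-up. The trial runs until "all clusters have crossed over to the intervention phase and delivered the intervention for at least 18 months", 35 months in total.

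Primary outcomes sets the intention-to-treat readout "at 12 months after the end of the transition period for each cluster". The effect is the sum of a step-change and a slope-change from a mixed model: "The model includes time since diagnosis in years, intervention (yes/no), and time since intervention in years". Baseline predictors may be added where appropriate. No calendar-time term is listed.

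The opening paragraph of Statistical analysis warns that "changes external to the trial may create underlying secular trends" and commits the analyses to a time adjustment whatever its p-value. It does not say what form that adjustment takes.

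**The concern.** The two sections do not match. One promises protection against secular change; the other lists the terms of the primary model and contains nothing that provides it.

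Time since diagnosis is the only background time variable listed. Within a patient it advances at the same rate as calendar time, so at best it absorbs a straight-line trend. It cannot represent a change at a particular date, such as a shift in general care, or a bend in the trend. Its single coefficient is also shaped by differences between patients diagnosed at different times, which are not calendar effects.

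This matters most late in the trial. After month 16 every observation is in transition or intervention, so the step and slope terms are free to absorb a common change that the listed model cannot place elsewhere. The conclusion at stake is whether a 12-month improvement in pain or quality of life can be attributed to the algorithm.

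**Working it through.** **Timetable.** Baseline 6 + five further steps of 2 months + transition 1 + intervention 12 + follow-up 6 = 6 + 10 + 1 + 12 + 6 = 35 months, which reproduces the stated total.

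- Clusters leave control at months 6, 8, 10, 12, 14 and 16.
- Transitions end at months 7, 9, 11, 13, 15 and 17.
- 12-month readouts (transition end + 12) fall at months 19, 21, 23, 25, 27 and 29.
- Longest exposure with a cluster still in control: 16 − 7 = 9 months.
- Largest difference in exposure between clusters at the same date after month 17: 17 − 7 = 10 months.

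**Share of a calendar change that enters the 12-month effect.** For fixed-effects matrix X, covariance V and calendar change s (1 at visits after the jump, otherwise 0), the expected generalised least squares estimate is (X′V⁻¹X)⁻¹X′V⁻¹s. The share is the sum of its step and slope-at-one-year elements.

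Inputs from the article: 6 clusters, the timetable above, scores every 3 months, 120 patients. Assumed, because Supplementary Appendix 5 is not shown: patient intercept variance 400, patient slope variance 0 to 400 per year², residual variance 300, cluster variance 0 or 20, entry in months 0 to 6 or spread over the control phase, transition scores dropped.

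| Change common to all clusters | Terms as listed | + linear calendar time | + categorical periods |
|---|---|---|---|
| Jump just after month 16 | 76–83% | 42–52% | 0 |
| Jump at month 20 | 68–71% | 31–49% | 0 |
| Jump at month 24 | 56–60% | 20–47% | 0 |
| Drift of 1 point/year from month 16 | 0.66–0.70 point | 0.25–0.54 point | 0 |

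Other assumptions (residual SD 15, time since diagnosis spread over 0 to 2 years at entry) give 72–74% for a month-18 jump under the listed terms. Across the assumptions tried, linear calendar time passes up to 54%.

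Time since diagnosis is a weak substitute even for a steady trend. Under the listed terms, a trend of 1 point per year through the whole trial added 0.90 to 1.14 points to the 12-month effect, because the coefficient is partly set by between-patient differences.

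**On the pain scale.** A 5-point jump (half the 10-point target difference, chosen only for scale) would contribute 0.55 × 5 = 2.8 to 0.83 × 5 = 4.2 points.

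**Precision.** With variances 400/100/300/0 and early entry, the standard error of the 12-month effect is 3.11 with the listed terms, 5.04 with linear time and 5.92 with categorical periods: 5.92 / 3.11 = 1.9. Across the variances in the table the ratio runs from 5.23 / 2.92 = 1.8 to 7.12 / 3.14 = 2.3. The other assumptions give ratios down to 5.2 / 3.4 = 1.5.

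To show what this could mean for power, suppose the listed model had exactly 90% power at two-sided 0.025. Then effect / SE = 2.241 + 1.282 = 3.523. Dividing by 1.5 gives 2.349 and power Φ(2.349 − 2.241) = 54%; dividing by 2.3 gives 1.532 and power Φ(1.532 − 2.241) = 24%. The stated power is above 90% and its model is not shown, so these figures are illustrations.

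**The case against.** The strongest reply is that Statistical analysis already commits to time adjustment, that a condensed article may leave its form to an analysis plan, and that the listed terms need not be exhaustive. Part of this stands: an unstated functional form would be no finding by itself. But the article does list the model, and the list omits what the other section promises. The choice is not cosmetic either, since linear and categorical adjustment differ widely in what they let through and both cost precision.

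A reader might infer something stronger: that because no cluster is in control at any 12-month readout, the result must be an uncontrolled before-after comparison that turns any late change into effect. The documents do not support that. The estimate is not a raw contrast at those months. Clusters differ in exposure by up to 10 months at the same date, through randomised timing, so period and exposure effects can be separated. The 12-month effect stays estimable even with free cluster, period and exposure-time effects. Even under the listed terms the jump enters in part, not in full.

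Nor do the documents support a specific false-positive rate, which would need both unseen variances and an invented shift.

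Recruitment could have led to longer steps (Safety and interim analyses). With other periods unchanged, a step above (19 − 6) / 5 = 2.6 months would let the first readout overlap with a control cluster. The 35-month total, and the Trial status dates (September 2020 to July 2023), fit 2-month steps.

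It is also tempting to let an analysis of months 0 to 16 with a single step effect decide the claim, because it uses only dates with a control cluster. That would be unsafe. The trial is sized on a slope change of 10 points over 365 days. For that effect, under assumed variances, such an analysis expects an estimate between about −0.1 and −1.5 with standard error 2.3 to 2.8. It points the wrong way in roughly 27 to 49% of trials and has about 2 to 5% power.

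**Conclusion.** The point holds in a limited form. Statistical analysis and Primary outcomes disagree on whether calendar time is in the primary model. If the model is fitted as listed, roughly 55 to 83% of a common calendar jump after month 16 would be reported as 12-month intervention effect, depending on its timing; with linear calendar time, about 20 to 54%; with categorical periods, none.

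The timetable follows from the documents alone. The shares and standard-error ratios rest on assumed variances, accrual and spread of time since diagnosis. They were worked out for a pain-type scale, and PANQOLI shares would follow its own variance ratios. The zero share under categorical periods requires period and exposure effects that are additive and common to all clusters. Nothing here shows that a secular change occurred; the plan itself treats it as a threat.

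**What to change.** 1. Reconcile the two sections by stating the calendar-time term in the primary model.
2. Pre-specify, for both co-primary endpoints and before analysis, a model on all data that keeps the step and slope terms and adds categorical calendar periods. Report its 12-month effect with a 97.5% interval beside the primary result.
3. State that if the two differ materially, the 12-month result will be described as not protected against secular change. Define what counts as material in advance.
4. Recheck the stated power with the calendar term included, using the variance parameters in Supplementary Appendix 5 and the actual number of patients in the primary analysis population.
5. An analysis of months 0 to 16 may be shown descriptively, but should not decide the claim.

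The cost is wording and one extra model per endpoint, with no new data. The real price is precision: the standard error of the 12-month effect is about 1.5 to 2.3 times larger under the assumed variances, so the categorical-period interval may be wide and should be presented with that caveat.

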### Primary endpoints

The co-primary outcomes of this study are QoL assessed with the Pancreatitis Quality of Life Instrument (PANQOLI) questionnaire and pain severity assessed according to the Izbicki pain score. PANQOLI is specifically developed and validated for the evaluation of QoL in CP and consists of four subscales: emotional function, role function, physical function, and “self-worth” [21]. This last subscale is unique, which differentiates PANQOLI from the previously applied questionnaires like the SF-12/SF36 and QLQ-C30/QLC-PAN26. Since there is no high-quality data on the dynamics of this score yet, QoL is also assessed by SF-36 in order to compare our results to previously performed studies. The Izbicki pain score consists of four questions regarding frequency of pain, intensity of pain (VAS-score), use of analgesics, and disease-related inability to work. Since there is a large spread in both QoL and pain severity scores among patients with different consequences for each patient’s perspective, both primary study endpoints will be evaluated separately as co-primary endpoints and not as a composite of both.

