### Sample size calculation

Sample size calculation is performed for the primary analysis population and is based on detecting the minimal clinically relevant difference (target difference) in the average PANQOLI scores and the Izbicki pain scores between the two study groups (current practice versus intervention). The protocol committee agreed by consensus on a clinically relevant difference of 10 points on the Izbicki pain score on average. Based on previously performed studies, we assumed a mean difference of 10% in QoL scores [22–24].

No high-quality data on the dynamics of PANQOLI scores have been reported yet; therefore, the Physical Component Summery scores of the SF36 (SF36_PCS) are used for simulations as being the best proxy. The intervention is considered successful if either or both pain and QoL scores improve. Therefore, to adjust for multiple testing, a two-sided alpha of 0.025 is used. We used data from the CARE registry to calculate our sample size [19]. The Izbicki pain score required a larger sample size as compared to SF36_PCS. This is mainly due to a larger within-patient variability of both intercept and slope. The model and parameters we used to determine the intra-patient variability and random error for the Izbicki pain score and to calculate the sample size are provided in Additional file 1: Supplementary Appendix 5. Based on this design, with 120 subjects the power to demonstrate an average slope change of 10 points reduction after 365 days is > 90%.

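### Cheap improvement, not an error: Holm's step-down could replace plain Bonferroni for the two co-primary endpoints at the same 5% family-wise error and with equal or higher power

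*Protocol article*

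**What the plan says.** Under Primary endpoints, the protocol article keeps the two outcomes apart: "both primary study endpoints will be evaluated separately as co-primary endpoints and not as a composite of both". Under Sample size calculation it sets the success rule: "The intervention is considered successful if either or both pain and QoL scores improve". It then draws the consequence for the error rate: "to adjust for multiple testing, a two-sided alpha of 0.025 is used".

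Under Statistical analysis, Primary outcomes, it names the method, "The Bonferroni correction method will be used to adjust for multiple testing", and fixes the threshold and the intervals: "For the co-primary endpoint, a two-sided alpha < 0.025 will be considered statistically significant" and "Effect estimates for the primary endpoints will be presented with 97.5% confidence intervals".

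The sections agree with each other. None mentions a step-down rule or passing alpha from one endpoint to the other. The SAP is not shown, but the method and the threshold are already fixed in the protocol, so this is not a detail left open.

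**The concern.** With two endpoints and an either-or-both claim, plain Bonferroni holds each endpoint to 0.025 whatever the other shows. Once one endpoint is significant at 0.025, the other can be tested at 0.05 without the family-wise error exceeding 5%. Suppose pain is clearly significant and PANQOLI has p = 0.03. The protocol would call PANQOLI non-significant, whereas a procedure with the same 5% guarantee would accept it.

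What is at stake is the conclusion on both outcomes. The formal rule needs only one, but the aim in the Abstract and the statement in the Discussion about a new standard of care both name quality of life together with pain. The second endpoint is also uncertain. PANQOLI was planned through an SF-36 proxy, and the Discussion recalls a trial in which less pain did not bring better quality of life.

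**Working it through.** **Inputs from the protocol.** Two endpoints; two-sided alpha 0.025 each; success on either or both; for the Izbicki score, "with 120 subjects the power to demonstrate an average slope change of 10 points reduction after 365 days is > 90" per cent. Also: "The Izbicki pain score required a larger sample size as compared to SF36_PCS". Planned power for the quality-of-life proxy is therefore at least as high.

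**Assumptions, not in the protocol.** Power of exactly 90% at 0.025 for both endpoints, and a correlation of 0 to 0.8 between the two test statistics. The variance parameters behind the power figure are in Supplementary Appendix 5, which is not shown, so that figure is taken as given.

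**1. The plan's own figure.** 0.05/2 = 0.025, which matches the threshold and the 97.5% intervals. With independent tests and no effect on either endpoint, the family-wise error is 1 − 0.975² = 0.0494.

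**2. Error under Holm.** Holm first compares the smaller p-value with 0.025, which is the Bonferroni test.
- No effect on either endpoint: the chance of any rejection is the same under both methods, 4.94% (correlation 0) to 4.02% (correlation 0.8).
- No effect on one endpoint, 90% power on the other: the true null is rejected in 2.5% of trials under Bonferroni and in 4.75% (correlation 0) to 4.08% (correlation 0.8) under Holm. Both are below 5%.

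**3. Power, by hand for correlation 0.** The critical values are 2.241 (0.025) and 1.960 (0.05). Power of 90% at 0.025 means a mean test statistic of 2.241 + 1.282 = 3.523. Power at 0.05 is then Φ(3.523 − 1.960) = Φ(1.563) = 0.941, so the chance of a p-value between 0.025 and 0.05 is 0.041.
- Bonferroni, both endpoints: 0.90² = 0.810.
- Holm, both endpoints: both p-values below 0.05, less the case in which both lie between 0.025 and 0.05: 0.941² − 0.041² = 0.884.
- Holm, one given endpoint: 0.90 + 0.041 × 0.90 = 0.937.
- At least one endpoint, either method: 1 − 0.10² = 0.990.

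**4. Power over the range of correlation** (exact bivariate-normal probabilities, 90%/90%):

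| Correlation | At least one (both methods) | Per endpoint, Bonferroni → Holm | Both endpoints, Bonferroni → Holm |
|---|---|---|---|
| 0 | 99.0% | 90.0% → 93.7% | 81.0% → 88.4% |
| 0.3 | 97.8% | 90.0% → 93.3% | 82.2% → 88.9% |
| 0.5 | 96.8% | 90.0% → 93.1% | 83.2% → 89.4% |
| 0.8 | 94.4% | 90.0% → 92.5% | 85.6% → 90.5% |

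The gain is 2.5 to 3.7 points per endpoint, 4.9 to 7.4 points for both, and nil for at least one.

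**5. Sensitivity to the assumed power** (chance of winning both):
- 90%/95%: 85.5% → 91.5% (correlation 0); 88.5% → 92.8% (0.8).
- 80%/80%: 64.0% → 75.1% (0); 68.7% → 77.8% (0.5); 72.9% → 80.4% (0.8).
- 90%/70%: 63.0% → 74.0% (0); 66.5% → 76.0% (0.5).

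Gains of about 9 to 11 points therefore need powers as low as 80%/80% or 90%/70%, with a correlation of at most about 0.5.

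**The case against.** The strongest reply is that nothing here is wrong. Bonferroni is valid, the sections agree, and choosing one valid method over another is partly preference. That stands, which is why this is offered as an improvement and not as an error.

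A reader might infer that the rule lowers the trial's chance of success or leaves it short of patients. The protocol does not support that. Success needs one endpoint, and the chance of at least one is identical under both methods. The power of more than 90% was computed at 0.025 and remains valid.

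A reader might also expect gains near ten points, or cite 70% power rising to 79% and 80% to 87%. Joint gains of that size need powers below those the protocol plans for. The marginal figures merely compare testing at 0.025 with testing at 0.05, and apply in full only if the other endpoint is certain to be significant. With 80%/80% and independence, power per endpoint rises to 85.5%, not 87%.

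Bonferroni has one real advantage: its 97.5% intervals are simultaneous and always agree with its tests. Under Holm, a second endpoint with p between 0.025 and 0.05 is significant although its 97.5% interval includes zero. Holm also uses more of the 5% when only one endpoint has an effect (step 2). Both points are fair, but the intervals can be kept and explained, and the error stays within 5%.

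Finally, the protocol was published after all clusters had crossed over, with 521 patients included. Relaxing a published threshold then requires a documented amendment before analysis.

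**Conclusion.** The point holds as a minor, optional efficiency gain. The specified method controls the family-wise error at 5%, and neither the formal success probability nor the sample size is affected. What Holm adds is a better chance of concluding on the second endpoint: about 5 to 7 percentage points for winning both and about 2.5 to 4 points per endpoint. These figures assume 90% power at 0.025 for both endpoints and a correlation of 0 to 0.8. The gain is smaller if power is well above 90%. It is larger if PANQOLI behaves less favourably than its SF-36 proxy, but that is an assumption about which the protocol gives no figure.

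**What to change.** Before outcome data are analysed, amend Primary outcomes to state that the smaller of the two co-primary p-values is tested at a two-sided 0.025 and, only if it is significant, the other at 0.05. Report Holm-adjusted p-values: twice the smaller p-value (capped at 1) for the first endpoint, and the larger of that value and the unadjusted p-value for the second. Keep the 97.5% intervals for both endpoints, with a note that the second endpoint's interval may include zero when its Holm test is significant.

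The cost is a sentence on the decision rule, a footnote and a dated amendment. No further patients, data or sample-size work are needed. If the change cannot be documented before analysis, the current rule should stay, because a switch made after seeing the results would not be credible.
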